### Randomization

Participants will be randomized to Wobenzym or placebo in a 1:1 ratio using a pre-generated randomization list with variable block sizes.

### Blinding

According to the randomization list the IMP (either Wobenzym or placebo) will be labelled with the participant’s ID by the manufacturer MUCOS GmbH and will be sent to the principal investigator.

### Participants safety

#### Adverse events

Adverse events are undesirable signs or symptoms that occur during the study and may or may not be causally related to the treatment. All adverse events considered at any level to be related to the IMP will be recorded on eCRFs. A common cold or URTI episode is not regarded as an AE in this study.

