## Methods

### Design and participants

Enzy-MagIC is a randomized, double-blind, placebo-controlled, monocenter phase I trial. Participants will be randomized in a 1:1 manner to receive either Wobenzym (treatment) or placebo. An overview of timing of randomization, treatment schema and data collection is presented in Figure 1.

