### Interventions

One week before the marathon race, the participants will begin daily ingestion (oral use) of the investigational product Wobenzym (3×4 tablets) and for the two weeks after the marathon race 3×2 tablets. The treatment schema can be seen in Figure 1. Both Wobenzym dosages prior and after the race are in accordance with recommendations in the patient information sheet. In case of heavy inflammatory illnesses or after acute trauma, the dosage can be increased up to 12 tablets per day. Therefore, 12 tablets per day prior to the race should serve as a loading dose before the marathon race representing a inflammatory stimulus. After this loading period, the dosage is decreased to a maintenance dosage of 6 tablets per day. Based on this dosage regime, an adequate plasma concentration of rutoside, trypsin and bromelain can be expected in accordance to the study of Roots et al. [42].

The study product is Wobenzym, an orally applied enzyme-rutoside combination supplement. Each tablet contains 90 mg bromelain, 48 mg trypsin, and 100 mg rutoside. The current indications of the investigational product are swelling and inflammation caused by injuries/trauma, thrombophlebitis and inflammation of joints due to osteoarthritis. Pharmacological investigations in animals have proven no toxic, teratogenic or mutagenic characteristics after single, multiple or long-term intake.

Wobenzym (formerly known as Phlogenzym®) has been on the German market since 1991. Typical adverse reactions of this oral enzyme therapy are a change of consistency, color and odor of the stool. At higher doses, sensations of fullness, flatulence and diarrhea may appear. These symptoms may also be related to the excipient lactose. Very few allergic reactions have been reported. All reported adverse reactions have been minor and disappeared after discontinuation. None of the cases required further treatment. The placebo supplement for the control group consists of lactose-monohydrate and has no active ingredient.

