#### Serious adverse events

Serious adverse events (SAEs) are defined as events that are fatal, life-threatening, disabling, incapacitating, or resulting in hospitalization, prolonged hospital stay, or malformation. All will be recorded in the eCRF, whether they are related to the IMP or not. According to preclinical data Wobenzym is a safe supplement. Any SAE considered at any level to be related to the IMP will be regarded as unexpected. All SAEs will be reported according to the GCP-guidelines.

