### Statistical methods

The difference of logarithmized IL-6 values will be calculated for each participant as distribution of IL-6 differences within the groups is expected to be skewed. Differences of logarithmized values will be compared between both study groups using a two-sample t-test. A two-sided level of significance of 5% will be considered for this primary efficacy analysis. Quantitative secondary endpoints will be analyzed using ANOVA methods, and qualitative data using chi-squared tests. Analysis of the primary endpoint and the secondary efficacy endpoints will be performed following the intention-to-treat (ITT) principle. These endpoints will also be assessed in the per-protocol dataset in the sense of sensitivity analyses.

The ITT dataset will consist of all trial subjects enrolled into the trial and randomized. For subjects with missing post marathon inflammation markers, a conservative replacement of the missing values will be conducted by imputing the lowest observed post marathon value for the placebo group and the highest observed value for the treatment group. The per-protocol dataset includes all trial subjects who were treated according to protocol. A tertiary dataset for analysis is the safety population. This population includes all trial subjects who received any IMP or other trial treatment.

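### Non-serious adverse events are entered on the eCRF only if judged related to the product, so all-cause rates by arm cannot be recovered

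*Protocol article*

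**What the plan says.** Under Participants safety, Adverse events, the protocol article opens with a definition that does not depend on causality: "Adverse events are undesirable signs or symptoms that occur during the study and may or may not be causally related to the treatment". The next sentence is the recording rule: "All adverse events considered at any level to be related to the IMP will be recorded on eCRFs". One exclusion follows: "A common cold or URTI episode is not regarded as an AE in this study".

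Under Serious adverse events the rule is the reverse: "All will be recorded in the eCRF, whether they are related to the IMP or not".

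Under Statistical methods a safety population is defined: "This population includes all trial subjects who received any IMP or other trial treatment". The design against which its events would be compared is stated under Design and participants: "Enzy-MagIC is a randomized, double-blind, placebo-controlled, monocenter phase I trial". No other section provides for recording non-serious events judged unrelated to the product.

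**The concern.** In a randomised, placebo-controlled trial, causality for common non-serious events is best judged by comparing arms. The recording rule puts an opinion on each individual event ahead of that comparison, and an event that fails the opinion is never entered. No later analysis plan can restore it.

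The setting makes this more than a formality. A marathon is a ready alternative explanation for many minor complaints. The Background and Discussion credit bromelain with reduced platelet aggregation and fibrinolytic activity, so minor bleeding or bruising is a plausible product effect that could easily be attributed to the race. At stake is the ability to see an excess of non-serious events that nobody expected. The primary IL-6 analysis is not affected.

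**Working it through.** **Reading the rule.** The word *only* does not appear in the recording sentence, so the restriction is an inference. Three statements side by side support it.

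| Item | Scope |
|---|---|
| Definition of an adverse event | related or unrelated |
| eCRF recording, adverse events | considered related at any level |
| eCRF recording, serious adverse events | all, related or not |

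Where the authors meant all-causality recording, they said so. The filter therefore applies to non-serious events.

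**Inputs.** The group size of 80 comes from the Sample size section. It reproduces for IL-6: with a log difference of |ln 0.75| = 0.2877 and a log SD of √ln(1 + 0.60²) = 0.5545, a noncentral-t calculation gives power 0.903 at 80 per group and 0.8998 at 79. The documents give no adverse event rate and no probability of an event being judged related. All such figures below are assumptions.

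**1. Same filter in both arms (blind intact).** Recorded rate = true rate × q, where q is the share of events judged related. Each participant is counted once. Power of a two-sided 5% test of two proportions is Φ[(d − 1.96·se₀)/se₁], with se₀ from the pooled rate and se₁ from the separate rates.

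For true rates of 30% v 15% and q = 1:
- d = 0.15 and the pooled rate is 0.225
- se₀ = √(2 × 0.225 × 0.775/80) = 0.0660
- se₁ = √((0.30 × 0.70 + 0.15 × 0.85)/80) = 0.0650
- power = Φ[(0.15 − 0.1294)/0.0650] = Φ(0.317) = 0.62

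| Share recorded (q) | Recorded rates | Expected counts per 80 | Risk difference | Power |
|---|---|---|---|---|
| 1.0 | 30% v 15% | 24 v 12 | 0.150 | 0.62 |
| 0.8 | 24% v 12% | 19.2 v 9.6 | 0.120 | 0.51 |
| 0.5 | 15% v 7.5% | 12 v 6 | 0.075 | 0.32 |
| 0.2 | 6% v 3% | 4.8 v 2.4 | 0.030 | 0.15 |

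The risk ratio stays at 2.0 throughout. With equal true rates, the same filter creates no difference. A second assumed pair, 40% v 20%, behaves alike: power 0.79 with full recording, 0.42 at q = 0.5 and 0.22 at q = 0.25.

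**2. Filter that depends on the type of event (blind intact).** Suppose expected gastrointestinal events are judged related 75% of the time and other events 10% of the time. Let true events per participant be 0.10 gastrointestinal + 0.10 other on placebo and 0.10 + 0.30 on treatment, a ratio of 0.40/0.20 = 2.0.
- Placebo recorded: 0.10 × 0.75 + 0.10 × 0.10 = 0.085
- Treatment recorded: 0.10 × 0.75 + 0.30 × 0.10 = 0.105
- Recorded ratio: 0.105/0.085 = 1.24

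Here the ratio shrinks too, because the excess lies in the events that nobody expected.

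**3. Filter that depends on the arm (blind partly lost).** With equal true rates of 20%, judging 25% v 50% of events related gives recorded rates of 5% v 10%, a spurious ratio of 2.0. A milder 30% v 40% gives 6% v 8%, a ratio of 1.33.

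**The case against.** The strongest reply is that the gap is narrow and the comparison remains fair.

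- **Threshold.** An event need only be considered related at any level. Under blinding that takes in merely possible relations. This stands: it makes the lower rows of the table less likely, but it does not bring the loss to zero.
- **Validity.** With an intact blind the same filter acts on both arms, so comparing the recorded events remains a valid randomised test of no difference. This stands, and it is why the harm is attenuation and missed events rather than false signals.
- **Other capture.** All serious events are recorded. Upper respiratory infections are collected through the WURSS-24, and muscular strain through the McGill questionnaire and muscle enzymes. The gastrointestinal reactions listed under Interventions are the ones blinded staff would most readily call related. All of this stands, so muscle pain and gastrointestinal upset are poor examples of what is lost. D-dimer, tPA and platelet aggregation are measured at every visit, but they do not record a bleed or a bruise.
- **Weight.** Safety is not a listed endpoint, the product has been marketed since 1991, and the article condenses a fuller protocol. The first two points limit the severity. The third does not answer the concern: the article states a rule, and the rule as stated excludes data.

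A reader might infer that the trial can give no unbiased safety comparison at all, or that no test could detect a filtered difference. The documents support neither. The serious-event comparison is intact, and the related-event comparison is valid under the blind. Low power is not zero power: 24 v 12 events gives a chi-squared p of about 0.02, and 5 v 2 gives about 0.25.

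A reader might also infer that the blind will fail, because "Typical adverse reactions of this oral enzyme therapy are a change of consistency, color and odor of the stool". That is only a possibility. The text also says that some gastrointestinal symptoms may come from lactose, and lactose is what the placebo consists of.

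**Conclusion.** The point holds for non-serious adverse events. As written, the protocol records such events only when they are thought related to the product, so all-cause rates by arm cannot be recovered in the safety population. The absolute between-arm difference shrinks in proportion to the share of events left out, and unexpected effects readily blamed on the race are the most exposed. On the assumed 30% v 15%, power falls from about 0.62 to between 0.51 and 0.15 as the recorded share goes from 80% to 20%. Those figures rest on assumed rates, one count per participant and the same filter in both arms, so they show direction and range and are not a forecast. Bias that depends on the arm needs partial unblinding, which the documents make possible but do not establish.

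The rule should be changed. Events that were never entered cannot be reliably retrieved later.

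**What to change.** Replace the recording sentence under Adverse events so that every adverse event from first intake of study product to visit 6 is entered on the eCRF, whatever its assessed relationship. Keep relatedness as a separate field, judged blind to allocation. Under Statistical methods, state that all-cause and related adverse events will each be tabulated by arm in the safety population. The serious-event rule and the separate handling of upper respiratory infections can stay as they are.

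The cost is a change of protocol wording and more eCRF entries over three weeks (one before the race, two after) for 160 men. No new visits or procedures are needed.

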#### Serious adverse events

Serious adverse events (SAEs) are defined as events that are fatal, life-threatening, disabling, incapacitating, or resulting in hospitalization, prolonged hospital stay, or malformation. All will be recorded in the eCRF, whether they are related to the IMP or not. According to preclinical data Wobenzym is a safe supplement. Any SAE considered at any level to be related to the IMP will be regarded as unexpected. All SAEs will be reported according to the GCP-guidelines.

#### Discontinuation

Participants have the right to withdraw from the clinical trial at any time and in any case without giving a reason. The investigator has the right to withdraw a subject for any reason which is in the best interests of the subject, including intercurrent illness or adverse events. Discontinued participants will not be replaced.

### Statistical methods

The difference of logarithmized IL-6 values will be calculated for each participant as distribution of IL-6 differences within the groups is expected to be skewed. Differences of logarithmized values will be compared between both study groups using a two-sample t-test. A two-sided level of significance of 5% will be considered for this primary efficacy analysis. Quantitative secondary endpoints will be analyzed using ANOVA methods, and qualitative data using chi-squared tests. Analysis of the primary endpoint and the secondary efficacy endpoints will be performed following the intention-to-treat (ITT) principle. These endpoints will also be assessed in the per-protocol dataset in the sense of sensitivity analyses.

The ITT dataset will consist of all trial subjects enrolled into the trial and randomized. For subjects with missing post marathon inflammation markers, a conservative replacement of the missing values will be conducted by imputing the lowest observed post marathon value for the placebo group and the highest observed value for the treatment group. The per-protocol dataset includes all trial subjects who were treated according to protocol. A tertiary dataset for analysis is the safety population. This population includes all trial subjects who received any IMP or other trial treatment.

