### Laboratory measurements

Blood samples will be collected 5-weeks (visit 1) and 1-week (visit 2) before the race, and immediately (visit 3), 24-h (visit 4), 72-h (visit 5) and 2 weeks (visit 6) after the race. At these visits inflammation measures (IL-6, IL-1-β, IL-10, myeloperoxidase, high-sensitivity C-reactive protein (hs-CRP), leukocyte count) will be analyzed.

Muscle damage parameters (creatine kinase (CK), myoglobin, glutamate oxalacetate (GOT), lactate dehydrogenase (LDH)) will be collected and measured at each visit (1-6). The short form of the McGill-questionnaire will be used to assess muscular strain [43].

Rheological parameters (D-dimer, tissue plasminogen activator (tPA), platelet aggregation) will be collected and measured at each visit (1-6).

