### Sample size

Sample size calculation was based on the primary endpoint criterion, the difference in marathon-induced change of plasma IL-6 between the study groups. Due to the expected right-skewed distribution of IL-6, differences in changes of logarithmized IL-6 levels (relative group changes) were considered as the base for inferential statistics. From previous publications a coefficient of variation (CV) of 0.60 for IL-6 changes was expected for the proposed study population [45]. Assuming a true relative difference of at least 25% between the groups, a sample size of 80 individuals per group is necessary to detect a difference in IL-6 changes between both groups (given the CV of 0.60) with a power of 90% on a two-sided level of significance of 0.05.

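### The primary t-test on change in log IL-6 is valid but fixes the baseline slope at 1; ANCOVA on the baseline already collected would be at least as precise, by an amount the article does not determine

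*Protocol article*

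**What the plan says.** The Statistical methods section of the protocol article defines the outcome and the test: "The difference of logarithmized IL-6 values will be calculated for each participant", and then "Differences of logarithmized values will be compared between both study groups using a two-sample t-test". On the error level it says: "A two-sided level of significance of 5% will be considered for this primary efficacy analysis". ANOVA methods are named only for quantitative secondary endpoints, and no section adjusts the primary comparison for baseline.

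The Sample size section plans on the same scale as the test. Its inputs are "a coefficient of variation (CV) of 0.60 for IL-6 changes was expected for the proposed study population" and "Assuming a true relative difference of at least 25% between the groups", leading to "a sample size of 80 individuals per group is necessary to detect a difference in IL-6 changes between both groups" "with a power of 90% on a two-sided level of significance of 0.05".

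Baseline data are available under Laboratory measurements: "Blood samples will be collected 5-weeks (visit 1) and 1-week (visit 2) before the race". Under Interventions, intake of the study product begins one week before the race. The article does not say which pre-race sample defines the change, nor whether the visit 2 sample is drawn before the first tablet.

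**The concern.** A change score is a regression of the post-race value on the baseline with the slope set to 1 in advance. If the true within-group slope differs from 1, subtracting the whole baseline leaves avoidable variance in the outcome. ANCOVA estimates the slope from the data. Under randomisation both analyses target the same quantity, the ratio of geometric means between groups, so choosing between them is a matter of precision.

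The analysis concerned is the single primary efficacy test. The plan has little reserve: power is close to 90% with all 160 participants, no inflation for dropout is stated, and under Discontinuation those who leave are not replaced. Precision that costs no extra visit or sample is worth having here.

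**Working it through.** **Reproducing the planned sample size.** Inputs from Sample size: CV 0.60, relative difference 25%, power 90%, two-sided 0.05.

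- Log-scale SD of the change, taking the changes as log-normal: sqrt(ln(1 + 0.60²)) = sqrt(0.3075) = 0.5545.
- Effect, reading 25% as a ratio of 0.75: ln(0.75) = −0.2877.
- Normal approximation: n = 2 × 0.3075 × (1.960 + 1.282)² / 0.2877² = 78.1, so 79 per group. The noncentral t gives 80.
- Power at 80 per group: 90.7% (normal), 90.3% (t).

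The stated 80 is reproduced. Reading the effect as ln(1.25) gives 130–131 and does not match.

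**Comparing the two analyses.** Let r be the within-group correlation of log baseline with log post-race IL-6, and k the baseline SD divided by the post-race SD. In units of the post-race variance:

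- Var(change) = 1 + k² − 2rk
- Var(ANCOVA) = 1 − r²
- Difference = (r − k)², which is never negative and is zero only when r = k, that is, when the slope r/k equals 1.
- Variance ratio = (1 − r²) / (1 + k² − 2rk); with equal SDs this is (1 + r)/2.

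**Power at 80 per group.** The article gives neither r nor k, so both are assumptions. The SD of the change is held at the planned 0.5545, data are complete, and ANCOVA has 157 degrees of freedom instead of 158.

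| k (pre/post SD) | r | slope r/k | variance ratio | power | n per group for 90% |
|---|---|---|---|---|---|
| 1 | 0.3 | 0.30 | 0.650 | 98.2% | 52 |
| 1 | 0.5 | 0.50 | 0.750 | 96.5% | 60 |
| 1 | 0.7 | 0.70 | 0.850 | 94.3% | 68 |
| 0.75 | 0.3 | 0.40 | 0.818 | 95.0% | 65 |
| 0.75 | 0.5 | 0.67 | 0.923 | 92.4% | 74 |
| 0.5 | 0.3 | 0.60 | 0.958 | 91.5% | 76 |
| 0.5 | 0.5 | 1.00 | 1.000 | 90.3% | 80 |
| 0.25 | 0.1 | 0.40 | 0.978 | 91.0% | 78 |

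Two rows by hand: k = 1, r = 0.3 gives 0.91/1.40 = 0.650; k = 0.5, r = 0.5 gives 0.75/0.75 = 1.

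**Cost when there is nothing to gain.** With a slope of 1, allowing for estimation of the slope (variance factor 1 + 1/156) lowers power from 90.3% to 90.2%, or 0.9034 to 0.9016, about 0.2 points.

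**Simulation check** (20,000 runs per scenario, t-test near 90% throughout): ANCOVA power was 98.1%, 96.2% and 94.0% for k = 1 with r = 0.3, 0.5 and 0.7; 91.1% for k = 0.5, r = 0.3; and 90.3% for k = 0.5, r = 0.5. These agree with the table to within a few tenths of a point.

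**The case against.** The strongest reply is that nothing is wrong. A t-test on log change is unbiased under randomisation, matches an endpoint worded as a change, and was sized on the variability of changes. All of that stands: the point concerns efficiency, not validity. It does not remove the case for a method that does no worse, apart from one degree of freedom, and may do appreciably better.

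The second reply concerns size, and it also stands. Power of 96–98%, or 52–60 per group, requires equal SDs before and after the race. If the race adds variance between runners, the post-race SD exceeds the baseline SD and the gain shrinks; at a post/pre ratio of 2 it is about one point or nothing.

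A reader might infer from the Background that the slope must be well below 1, because post-exercise IL-6 depends on workload. The Background says only that the increases are related to workload. It gives no correlation and no slope, and a low correlation with a large SD ratio can still produce a slope near 1.

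A reader might also say that chance baseline imbalance biases the t-test. Averaged over randomisations it does not. Imbalance is part of the variance already counted and is reflected in the standard error, so it is not a second defect.

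Finally, the planned imputation gives every participant with a missing post-race marker one extreme value for his group, unrelated to his own baseline. This changes both the correlation and the post-race SD, so the complete-data figures do not carry over exactly to the intention-to-treat analysis.

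**Conclusion.** The point holds as a recommendation to improve efficiency. The planned test is valid and reaches its planned power on the article's own inputs; the documents do not support a claim that the trial is underpowered or that its primary result would be biased by this choice. What can be said is that ANCOVA on log baseline targets the same ratio, is asymptotically never less precise, and costs at most about 0.2 points of power.

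The benefit cannot be derived from the article. On complete data, with the SD of change at 0.5545 and a true ratio of 0.75, it runs from none (slope of 1) through about one point to power of 94–98% with equal SDs and correlations of 0.7 to 0.3. No single figure in that range should be presented as the expected gain, and none of them justifies reducing the sample size.

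**What to change.** Make the primary analysis an ANCOVA of ln IL-6 at visit 3 (immediately after the race) on treatment group, with ln pre-treatment IL-6 as covariate, reported as an adjusted geometric mean ratio with 95% confidence interval. Keep the two-sample t-test on log change as a sensitivity analysis.

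Name the covariate in advance. Visit 1 is clearly before treatment. Visit 2, or the mean of ln visit 1 and ln visit 2, is suitable only if the visit 2 sample is drawn before the first tablet, which the text should state. This also settles which pre-race sample is the baseline.

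The change takes a sentence or two in Statistical methods and should be made before unblinding. It needs no further samples or participants and uses one degree of freedom.

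### The primary ITT analysis of IL-6 fills missing post-race values with opposite extremes by arm, so the stated 90% power and two-sided 5% level hold only with essentially complete data

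*Protocol article*

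**What the plan says.** All statements are in the Protocol article.

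- **Analysis set (Statistical methods).** The primary endpoint follows ITT: "The ITT dataset will consist of all trial subjects enrolled into the trial and randomized".
- **Missing values (Statistical methods).** For men without post-race inflammation markers, "a conservative replacement of the missing values will be conducted by imputing the lowest observed post marathon value for the placebo group"; the treatment arm receives the highest value instead.
- **Test (Statistical methods).** Each man's difference in log IL-6 enters a two-sample t-test. "A two-sided level of significance of 5% will be considered for this primary efficacy analysis".
- **Sensitivity (Statistical methods).** The per-protocol dataset is the only alternative analysis named.
- **Power (Sample size).** "a sample size of 80 individuals per group is necessary to detect a difference in IL-6 changes between both groups", "with a power of 90% on a two-sided level of significance of 0.05".
- **Losses.** Design and participants recruits 160, exactly twice 80. Discontinuation states that men who leave are not replaced. No rate of drop-out or missed samples appears anywhere.

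**The concern.** An opposite-extremes rule is normally a stress test. Here it is the primary handling of missing data. Each imputed value lies in the far tail of its arm, always in the direction that disfavours the product, and is then tested as if it had been measured. Three things follow as the number of missing samples grows: the estimated effect is pulled towards harm, the within-arm variance is inflated, and one outlying runner per arm can fix the value given to every missing man in that arm.

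The power statement takes no account of this, and the two-sided error rate no longer holds. A product that works as assumed could be reported as ineffective, and an inert product could be reported as raising IL-6. The per-protocol analysis does not repair this, because it is a secondary check in a selected set.

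**Working it through.** **Inputs.** Two-sided 5% and 90% power (Sample size). "Assuming a true relative difference of at least 25% between the groups", read as a ratio of 0.75. "a coefficient of variation (CV) of 0.60 for IL-6 changes was expected for the proposed study population". 80 per group. "Participants will be randomized to Wobenzym or placebo in a 1:1 ratio".

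**Step 1: reproduce the plan's figure.**
- Log SD = sqrt(ln(1 + 0.60²)) = sqrt(ln 1.36) = 0.5545.
- Effect = |ln 0.75| = 0.2877.
- n per group = 2 × (1.960 + 1.282)² × 0.5545² / 0.2877² = 78.1, so 79 by the normal approximation. The noncentral t gives 80, with power 90.3% at 80.

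The stated sample size is sound, but it assumes that all 160 men have a measured change.

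**Step 2: size of the shift.** In about 76 to 79 normal observations the expected extreme lies about 2.4 SD from the mean. One missing man in each arm therefore places two imputed values 2 × 2.4 = 4.8 SD apart beyond the true difference. In log units this is 4.8 × 0.5545 = 2.66. Spread over 80 men it shifts the mean difference by 2.66 / 80 = 0.033 per missing pair. The assumed effect is cancelled at 0.2877 / 0.033 = 8.7, that is, between 8 and 9 missing per arm.

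**Step 3: simulate the stated rule.** 80 per arm, normal log changes, values missing completely at random, equal numbers missing per arm, imputation as stated, then the t-test. The base case takes each arm's own extreme on the change scale (100,000 trials per cell).

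The ranges cover this and three further readings, because the article does not say whether extremes are within arm or pooled and gives no pre- and post-race SDs:
- extremes pooled over both arms;
- imputation on the log post-race value, with an assumed baseline log SD of 0.5 and change independent of baseline;
- the same, with an assumed baseline log SD of 0.35 and pre- and post-race values independent.

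| Missing per arm | Power, true ratio 0.75 | Mean estimated ratio | Significant harm, inert product |
|---|---|---|---|
| 0 | 90% | 0.75 | 2.5% |
| 1 | 80% (74-83%) | 0.78 | 5% (4-6%) |
| 2 | 66% (52-74%) | 0.80 | 10% (8-12%) |
| 4 (5%) | 34% (15-49%) | 0.86 | 26% (18-36%) |
| 8 (10%) | 4% (0.1-12%) | 0.98 | 73% (55-88%) |

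The ratio column is exp(mean difference): exp(-0.154) = 0.86 with 4 missing and exp(-0.023) = 0.98 with 8.

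**Step 4: other conditions.**
- *Benefit real (ratio 0.75).* Significant harm is 0.7% in the base case with 8 missing per arm, and at most about 4% under any of the four readings up to that number.
- *Inert product, false benefit.* Falls from 2.5% to 0.3% with 2 missing per arm and 0.03% with 4.
- *Unequal missingness.* Four missing in one arm only gives 66% power; 2 against 6 gives 34%.

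**Step 5: is it the imputation or the lost numbers?** Analysing only the observed men, under the same assumptions, gives power of 89.6%, 88.8% and 87.1% with 2, 4 and 8 missing per arm, and the two-sided level stays at 5%. The imputation causes the loss.

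**The case against.** The strongest defence is that the rule does what its label says. The trial's hypothesis is directional, and the rule makes a false claim of benefit very unlikely. That stands, and it is a reason to keep the rule as a sensitivity analysis. It does not rescue the primary analysis, which is declared two-sided at 5% and also has to deliver an estimate.

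Secondly, the amount of missing data is unknown. Participants must already have finished a half marathon and must intend to run this race, so losses could be low; with 1 missing per arm, power is still about 80%. A reader might infer that several missing samples are all but certain in a marathon study. The article supports no rate, so the table can only be read conditionally.

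Other stronger readings also go too far:

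- *That the rule generally produces false harm.* This needs an absent or small true effect (Step 4).
- *That a working product would probably be missed.* This needs about 3 or more missing per arm, where base-case power is 50%.
- *That men who never start receive the most extreme change in both arms.* This fits the treatment arm. If IL-6 rises after the race, the value given to placebo non-starters is the observed one nearest to no change.
- *That matters are worse still if the extremes are taken over all post-race visits.* Sizing this needs the fold rise in IL-6, which the article does not give.

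**Conclusion.** The point holds in conditional form. The rule as written is the primary handling of missing IL-6 data. With it, the stated power and two-sided error rate are true only if almost no man lacks a post-race value. At 5% missing per arm, power for the assumed effect is roughly one third and, under every reading tried, below one half. With an inert product, the harm rate at that level is about ten times nominal (26% against 2.5%). The estimated ratio is biased towards no effect, reaching about 0.98 at 10% missing when the truth is 0.75.

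This rests on normal log changes, values missing completely at random, equal numbers missing per arm unless stated, and assumed missingness rates. The base-case figures should be quoted with their ranges. The sample size itself is not at fault.

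**What to change.** Before unblinding, state in the protocol or SAP that the primary IL-6 analysis is likelihood-based or uses multiple imputation under missing at random. It should be on the log scale, in all randomised men, and use the pre-race and other post-race samples already scheduled. Keep the opposite-extremes rule as a labelled sensitivity analysis, saying whether extremes are within arm or pooled, or replace it with a graded delta (tipping-point) analysis.

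The cost is a few sentences and no new data. The price is that the primary result then depends on missing at random. That is doubtful for men who drop out during the race. Later samples may also predict the immediate value poorly, since the Background section says that IL-6 falls quickly after exercise. The retained worst-case or delta analysis covers this.

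Restricting the analysis to men who started the race would change the stated ITT set. It should appear only as a labelled supplementary analysis.
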